#### Secondary outcomes

The rate of response (decrease of MADRS score by 50 %), and rate of relapse (MADRS >12 after remission of the index episode) at 15 months after inclusion will be analyzed with the similar method used for the main criterion.

A mixed-model will be used to analyze:Variations (intra- and between-group) of depression intensity using MADRS and BDI scores between inclusion, and at 3, 6, 9 and 15 months after inclusion.And model the evolution of MADRS and BDI scores during follow-upVariations (intra- and between-group) of global functioning (using the FAST) between inclusion, and at 9 and 15 months after inclusion,Variations of quality of life using WHOQOL-26 scale between inclusion, and at 9 and 15 months after inclusion,

The rate of relapse (MADRS >12 after remission of the index episode) at 15 months after inclusion, the rate of hospitalization during follow-up and the discontinuation rate of antidepressant therapy at 15 months after inclusion will be analyzed using a chi-square test or Fisher’s exact test if the chi-square is not valid.

The between-group comparison on variation in treatment adherence using MARS and changes in benzodiazepines doses between inclusion and 15 months post inclusion will be performed using the student-t test if distribution is normal or the Mann–Whitney test, if otherwise.

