### Sample size

For the control group the full remission rate at 15 months is expected to be 30 % [48]. If, in the experimental group, this rate is 15 % higher, with a power of 0.80 and a two-tailed significance level at 0.05, the sample size ends up to 166 patients per group. Because loss to follow-up will be considered as “not in remission”, no adjusted sample size for taking dropouts into account has to be established. Thus, a total number of 332 subjects will be enrolled in the study. Each center will recruit between 20 and 40 patients: one to 2 psychoeducational groups of 8–10 patients and 10–20 patients in the control group.

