### Participants and procedure

#### Inclusion and exclusion criteria

We will include outpatients [1] aged 18–65 years [2] with a main diagnosis of non-psychotic non-chronic (<2 years) major depressive episode (DSM-IV criteria) of moderate to severe intensity (Montgomery Asberg Depression Scale score >24) [49] taking at least one antidepressant [4] able to speak, read and understand French [5] and able to give written informed consent.

We will exclude subjects [1] with a current diagnosis of substance abuse or dependence in the 6 months prior to inclusion, excluding tobacco, [2] current psychotic features, [49] duration of current depressive episode >2 years, [4] current organic mental disorder or mental retardation, or severe comorbid medical condition, [5] lifetime history of schizophrenia, or schizoaffective or bipolar disorder, manic, hypomanic, or mixed episodes according to DSM-IV criteria, [6] sensory or cognitive disabilities, [7] hospitalized full-time at the time of inclusion, [8] having a relationship or being employed by the sponsor or investigator. We will also exclude patients who are planning a long stay outside the region preventing compliance with the scheduled visits, and subjects participating in another trial.

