#### Eligibility assessment and randomization

People who apply for participation in the study will receive an information letter with comprehensive details on study procedures. Signed written informed consent will be obtained from all participants. They will be informed that they can withdraw from the intervention and/or study at any time without any negative consequences.

The first visit will consist in evaluating the following data:○ Sociodemographic characteristics: age, gender, nationality, marital status, educational level, employment status;○ Psychopathology using the Mini-International Neuropsychiatric Interview (M.I.N.I.) [50];○ Number of previous depressive episodes, date of onset of the current episode;○ Depression intensity using the Montgomery Asberg Depression Scale (MADRS) and Beck Depression Inventory (BDI);○ Global functioning using the Functioning Assessment Short Test (FAST);○ Quality of life using the World Health Organization Quality Of Life measure-26 (WHOQOL-26) scale;○ History of psychotropic treatment (name, dose);○ Treatment adherence using the Medication Adherence Rating Scale (MARS);○ Lifetime suicidality using the Columbia–Suicide Severity Rating Scale (C-SSRS).

All inclusion and non-inclusion criteria will be checked by the study investigator. Patients will then be informed of their eligibility and randomized with the Capture Software System (Clinsight). Randomization will be performed with a permuted-block 1:1 ratio randomization list with varying block sizes and will be stratified in participating centers. Allocation concealment will be achieved by a centralized randomization procedure via an electronic case-report form.

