#### Treatment as usual

Treatment as usual will consist of the usual clinical management of depression including psychiatric evaluation and adaptation of pharmacological treatment. There will be no treatment restriction during the study period. The current pharmacological treatment will be recorded at each visit.

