#### Secondary endpoints

Variation of the depression intensity between baseline, and at 3, 6, 9 and 15 months after inclusion using MADRS and Beck Depression Inventory (BDI) [60, 61];Evolution of MADRS and BDI scores during follow-up;Response rate (50 % decrease in MADRS score) at 15 months after inclusion;Relapse rate (MADRS >12 after remission of the index episode) at 15 months after inclusion;Hospitalization rate during follow-up;Variation of global functioning, using the Functioning Assessment Short Test (FAST) [62], between baseline, and at 9 and 15 months after inclusion;Variation of quality of life using the World Health Organization Quality Of Life measure-26 (WHOQOL-26) scale [63] between baseline, and at 9 and 15 months after inclusion;Variation of treatment adherence using the Medication Adherence Rating Scale (MARS) [64] between baseline and 15 months after inclusion;Variation of benzodiazepines doses between baseline and at15 months after inclusion;Discontinuation rate of the antidepressant treatment at 15 months after inclusion.

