### Statistical analysis

#### General statistical considerations

All statistical analyses will be performed using SAS® (SAS Institute, Cary, NC, USA).

For efficacy variables, we will use a Full Analysis Set, which will include all randomized subjects with a valid primary efficacy baseline measurement and at least one valid primary efficacy measurement. A robustness evaluation using the Completer Set (CS) will also be performed for the primary efficacy variable. The CS is a subset of the FAS and will include all subjects with a valid measurement at the end of the study Period (15 months) for the primary efficacy variable.

A summary of demographic data and baseline characteristics, as well as medical and procedure history will be presented for the whole population (all treatment groups combined) and for each treatment group. For continuous variables, summary statistics (n [number of available measurements], arithmetic mean, standard deviation [SD], median, interquartiles, minimum, and maximum) will be tabulated. For descriptive statistics of continuous variables, change from baseline and each time point will be displayed.

Frequency tables (frequency counts and percentages) will be presented for categorical data.

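### The benzodiazepine dose comparison pools baseline users and non-users in one unstratified test; stratifying by use at inclusion would gain sensitivity at almost no cost (minor)

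*Protocol article*

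**What the plan says.** All places are in the protocol article.

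- **Endpoint.** Secondary endpoints, under the efficacy endpoints, lists "Variation of benzodiazepines doses between baseline and at15 months after inclusion". It names no subset of patients.
- **Test.** Secondary outcomes, in the statistical analysis, says that the between-group comparison of "changes in benzodiazepines doses between inclusion and 15 months post inclusion will be performed using the student-t test if distribution is normal", with Mann-Whitney as the alternative. No stratum or covariate is named.
- **Population.** General statistical considerations defines the set in which efficacy is analysed: "we will use a Full Analysis Set, which will include all randomized subjects with a valid primary efficacy baseline measurement". Patients must also have one or more usable values of the primary measure. Benzodiazepine use plays no part in it.
- **Eligibility.** Inclusion and exclusion criteria asks for patients "taking at least one antidepressant". It does not ask for a benzodiazepine.
- **Data.** The first visit records psychotropic drugs by name and dose (Eligibility assessment and randomization). For follow-up, Treatment as usual says: "The current pharmacological treatment will be recorded at each visit".

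**The concern.** Read together, these sections put two kinds of patient into one test. A patient on a benzodiazepine at inclusion can go down, stay or go up. A patient not on one can only stay at zero or start. The pooled change therefore has a spike at zero, which makes normality unlikely and leaves the Mann-Whitney ranks heavily tied. Randomization is stratified by centre only, so the number of baseline users can differ between arms by chance, and that difference goes into the error term.

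The stake is limited but real. Modification of psychotropic treatment is a stated secondary objective, and only this endpoint and antidepressant discontinuation carry it. A less sensitive test makes it more likely that a true change is reported as no difference. A single pooled p-value also does not show whether users stopped or non-users started.

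**Working it through.** **1. The plan's own figure.** The only sample-size calculation is for remission: "For the control group the full remission rate at 15 months is expected to be 30" %, and "If, in the experimental group, this rate is 15 % higher", so 30% against 45%, two-sided 0.05, power 0.80.

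n = [1.960 × √(2 × 0.375 × 0.625) + 0.842 × √(0.30 × 0.70 + 0.45 × 0.55)]² / 0.15² = (1.342 + 0.569)² / 0.0225 ≈ 162.3, so 163 per group.

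The stated 166 is within 3 of this and gives power 0.809. It reproduces, and it says nothing about benzodiazepines. I use 166 per arm below.

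**2. Ties and imbalance.** Let q be the share of baseline users (not in the documents; assumed 30% to 70%).
- Non-users per arm: 166 × (1 − q), which is 116 at q = 0.3 and 50 at q = 0.7. If 5% of them start (assumed), about 110 and 47 per arm have a change of exactly zero.
- Chance difference in the number of users between arms, ignoring centre strata: SD = √(2 × 166 × q(1 − q)) = √83 ≈ 9 patients at q = 0.5.

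**3. Dilution of the mean.** If users differ between arms by d (in SD of users' change) and non-users stay at zero, the pooled mean difference is q × d. The pooled variance per arm is q + q(1 − q)m², where m is that arm's mean change among users.

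Example: q = 0.3, d = 0.5, control users falling 0.5 SD.
- Variances: 0.30 + 0.21 × 0.25 = 0.3525 and 0.30 + 0.21 × 1 = 0.51.
- SE = √(0.8625 / 166) = 0.072.
- Pooled t-test power = Φ(0.15 / 0.072 − 1.96) = 0.55, against 0.70 in users alone.
- Mann-Whitney by simulation: 0.41 pooled, 0.68 in users alone.

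Over q = 0.2 to 0.9, d = 0.4 or 0.5, and control users either stable or falling 0.5 SD, the loss is about 0 to 16 points for the t test and 0 to 27 for Mann-Whitney. It is largest when users are few and about 2 points at most at q = 0.9. This shows the dilution only. A users-only analysis would drop the new starts, so it is not the proposed replacement.

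**4. The pooled test against a stratified test on all patients.** Simulation, 166 per arm, 1,500 runs (Monte Carlo SE about √(0.25 / 1500) = 1.3 points at 50% power), 5% of non-users starting, doses taken to be on a common scale. Power of the pooled Mann-Whitney test, then of van Elteren stratified by baseline use:

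| Assumed effect | 30% users | 50% users | 70% users |
|---|---|---|---|
| Stopping 40% to 60% | 17% to 28% | 37% to 53% | 58% to 69% |
| Mixed: stopping 30% to 42%, halving 20% to 35% | 21% to 29% | 41% to 52% | 61% to 69% |
| Halving 20% to 50%, stopping 40% in both arms | 17% to 18% | 29% to 31% | 43% to 45% |

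Null rejection was about 5-6%. Results move by several points with inputs that nobody can fix from the documents, such as the dose spread and background stopping:
- The most favourable set, at 50% users, gave 35% to 53% for stopping and 44% to 48% for halving.
- Another set gave 36% to 49% for stopping and 33% against 31% for halving, so no gain there.
- The more cautious summary, which I adopt, is a gain of about 9-13 points for stopping, about 4-8 for a mixed effect, and a difference within about 2 points for pure halving, with type I error near 5%.

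**The case against.** The strongest reply is that nothing here is an error. Comparing all randomized patients is unbiased, respects the randomization and counts new starts as well as reductions. It fits an objective worded as modification of treatment, not reduction among users. A rank test is already planned for non-normal data. The endpoint is secondary and the trial was not sized for it. All of this stands, and it is why the point is minor.

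It is also fair that the gain depends on the pattern of effect and that every input is assumed. That stands too: the stratified test is not best in every scenario. It also leaves power modest, at about 28% with 30% users even when the effect is on stopping. So a missed reduction cannot be blamed on pooling alone. What the reply does not meet is that stratifying keeps all patients, holds the error rate, costs nothing material, and in these runs was at worst about 2 points behind.

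A reader might go further and infer that raw milligrams of different molecules are compared, so that a switch of molecule is scored as a dose change. The documents do not support that. They speak of doses without a unit, and the drug name recorded at the first visit is part of what a conversion needs. A dose-equivalence table and the handling of switches are usual content of a full protocol or SAP, neither of which is shown.

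**Conclusion.** As written, one unstratified t or Mann-Whitney test is applied to a set that mixes baseline users and non-users. This costs sensitivity and makes the result harder to read, but it does not make the test invalid or biased. Under assumed inputs (166 per arm, 30-70% users), the avoidable loss is about 9-13 points of power for an effect on stopping, about 4-8 for a mixed effect and essentially none for pure dose-halving. These figures are illustrative, because the documents give no benzodiazepine prevalence, dose spread or expected effect. Grade: minor. The sample size and the primary conclusion are unaffected.

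**What to change.** In Secondary outcomes, replace the pooled Student t or Mann-Whitney test for the benzodiazepine dose change with a rank test stratified by benzodiazepine use at inclusion (van Elteren), on all analysed patients. Beside it, report by arm, with 95% confidence intervals, the share of baseline users who had stopped at 15 months and the share of baseline non-users who had started.

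The cost is a few lines of analysis wording, fixed before any comparison by arm. The stratum comes from the drug history taken at the first visit, and the two shares come from the treatment recorded at each visit, so no new data are needed.

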#### Safety analyses

For the analysis of safety data (AEs, vital signs), RS will be used. Adverse events occurring during this study will be presented by system organ class (SOC), high level term (HLT), and preferred term [65] in a frequency table giving the number of events, number of subjects, and percentage of subjects who experienced the event by treatment group.

Subjects with multiple AEs will be counted only once within each PT, HLT, and SOC. Coding of the AEs will be performed with the Medical Dictionary for Regulatory Activities.

Vital signs variables and their changes from Baseline will be presented using descriptive statistics by visit and treatment group.

Rate of suicidal behaviors (completed suicide and suicide attempts) at 15 months after inclusion, variation of severity and intensity of suicidal ideations subscores between inclusion and at 3, 6, 9 and 15 months after inclusion will be reported for each group.

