## Endpoints

### Safety endpoints

Incidence, relatedness, and severity of treatment-emergent adverse events will be evaluated at each visit until the end of study. Safety parameters assessed in this clinical trial will be recorded and evaluated through repeated clinical examinations of the patients. It relies on assessment of suicidality using the Columbia–Suicide Severity Rating Scale (C-SSRS) [59]: rate of suicidal behaviors (completed suicide and suicide attempts) at 15 months post inclusion, variation of severity and intensity of suicidal ideations subscores between baseline and at 3, 6, 9 and 15 months after inclusion. If a patient exhibits a high-risk of suicide (increased suicide ideations, planning a suicide attempt) during a visit, investigators will contact the psychiatrist in charge of this patient.

Moreover, acceptability will be assessed. It will consist in the number of missed sessions, and satisfaction at 3 months post inclusion using a Likert scale ranging from 0 (not useful at all) to 10 (extremely useful) for the intervention group.

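### Suicidal-ideation safety is defined only as per-arm change in C-SSRS subscores, which is insensitive to a minority who worsen and may mask an excess in the ENVIE arm if that arm also has more improvers

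*Protocol article*

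**What the plan says.** The Safety endpoints section bases safety on the C-SSRS and names two elements. One is the rate of suicidal behaviours. The other is "variation of severity and intensity of suicidal ideations subscores between baseline and at 3, 6, 9 and 15 months after inclusion". The Safety analyses section repeats both: "Rate of suicidal behaviors (completed suicide and suicide attempts) at 15 months after inclusion", and the ideation element, by arm, as "variation of severity and intensity of suicidal ideations subscores between inclusion and at 3, 6, 9 and 15 months after inclusion will be reported".

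Under General statistical considerations, continuous variables get "arithmetic mean, standard deviation [SD], median, interquartiles, minimum, and maximum) will be tabulated", and "For descriptive statistics of continuous variables, change from baseline and each time point will be displayed". Categorical data get counts and percentages. The article does not say which class the ideation subscores belong to.

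The Safety endpoints section also has a patient-level trigger: "If a patient exhibits a high-risk of suicide (increased suicide ideations, planning a suicide attempt) during a visit", the investigators contact the treating psychiatrist. No section says that these patients are counted by arm.

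Adverse events are presented in a "frequency table giving the number of events, number of subjects, and percentage of subjects who experienced the event by treatment group". The hospitalisation rate is a secondary endpoint compared between arms.

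**The concern.** Elsewhere the article keeps two words apart. Change in a score (MADRS, BDI, FAST, WHOQOL-26, MARS) is called variation and is analysed by a mixed model, a t-test or a Mann-Whitney test. Patient-level events (remission, response, relapse, hospitalisation, suicidal behaviour) are called rates. Ideation is placed in the first class, so the natural reading is a summary of change in score per arm.

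Such a summary nets gains against losses. Patients enter with MADRS above 24, so many have room to improve, and the trial is designed to find more benefit under ENVIE: the Sample size section assumes 15 points more remission, and the Background and Discussion cite an effect of ACT on suicidal risk. If the programme helped more patients than the waiting list while making some worse, the average change could look equal or better in ENVIE. The protocol treats an individual's increased ideation as a high-risk event at the visit, yet the planned tables would not say how many patients had one in each arm.

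**Working it through.** **The plan's own figure.** No figure is given for the ideation endpoint. The only one needed is the arm size of 166. With 30% versus 45% remission, two-sided 0.05 and power 0.80, the pooled formula gives n = [1.96·√(2·0.375·0.625) + 0.8416·√(0.30·0.70 + 0.45·0.55)]² / 0.15² = (1.342 + 0.569)² / 0.0225 ≈ 162.3, so 163 per arm. Power at 166 is 0.809. The stated 166 is consistent with this and is used below.

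**Illustrative model (all rates and the step size are assumptions; the article gives none).** Each patient's ideation score changes by −2 (improved), 0 or +2 (worsened), with shares a improved and w worsened.
- Mean change: m = −2a + 2w
- Variance: v = 4(a + w) − m²
- SE of the difference in means: √[(v₁ + v₂)/166]
- Chance that ENVIE's mean is significantly worse: Φ(d/SE − 1.96), with d = ENVIE mean minus control mean
- Comparator: power of a two-sided 0.05 test on the proportion worsened, 166 per arm

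The article plans no test of either quantity. The probabilities only measure how much each summary can show.

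Control is fixed at 50% improved and 5% worsened: m = −0.90, v = 4(0.55) − 0.81 = 1.39.

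| ENVIE improved / worsened | ENVIE mean | d | Chance mean is significantly worse | Power on proportion worsened |
|---|---|---|---|---|
| 50% / 10% | −0.80 | +0.10 | 0.11 | 0.41 |
| 50% / 15% | −0.70 | +0.20 | 0.28 | 0.86 |
| 60% / 15% | −0.90 | 0 | 0.025 | 0.86 |
| 65% / 15% | −1.00 | −0.10 | below 0.01 | 0.86 |

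Second row in full: v = 4(0.65) − 0.49 = 2.11; SE = √(3.50/166) = 0.145; 0.20/0.145 − 1.96 = −0.58; Φ = 0.28. In the last row the mean favours ENVIE while expected worsening triples, from 166 × 0.05 ≈ 8 to 166 × 0.15 ≈ 25 patients.

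**Would the other descriptive statistics reveal it?** Take ENVIE 50% improved and 12% worsened, control 40% and 4%.
- Means: −0.76 and −0.72. Difference −0.04, SE = √[(1.902 + 1.242)/166] = 0.138, 95% CI −0.31 to 0.23.
- Worsened: 20/166 versus 7/166. Risk difference 7.8 points, 95% CI 2.0 to 13.7, Fisher p = 0.015.
- In both arms the lower quartile is −2, the upper quartile 0 and the maximum +2.
- Median: −1 in ENVIE and 0 in control, again favouring ENVIE.
- SD: √1.902 = 1.38 and √1.242 = 1.11. This is the only statistic that hints at a difference, and a wider spread does not identify harm.

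In this model an upper quartile cannot register a worsening group smaller than 25%, and a maximum can reflect a single patient. Separate summaries at each visit also cannot give the number who worsened at any visit.

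**The case against.** A reader might infer that a harm signal in the ENVIE arm would not show at all, because most patients improve. The article does not support that. Improvement common to two randomised arms does not cancel a difference between them: with 50% improving in both and 5% versus 15% worsening, the means are −0.90 and −0.70, visibly worse for ENVIE. Complete masking needs correspondingly more improvers in ENVIE.

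A reader might also infer that suicides and attempts are the only patient-level safety counts. They are not: adverse events are tabulated by number and percentage of subjects per arm, and hospitalisation is compared by arm. Nothing states, however, that a rise in C-SSRS ideation or the high-risk trigger is recorded as an adverse event, so those routes are not assured for ideation.

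The strongest objection is that the article never says the subscores will be averaged. Per-arm reporting of variation could include a table of improved, unchanged and worsened patients, and the full protocol or SAP, neither shown, may contain one. That limits how firmly the point can be pressed. It does not remove it: the endpoint is worded the same way in two sections, and the article's own usage makes variation a change in score and not a count.

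Nor is the remedy free. The Eligibility assessment and randomization section lists the C-SSRS at the first visit for lifetime suicidality, so the article does not show that a recent baseline rating exists. A count over any visit also depends on how many visits each patient attends.

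**Conclusion.** The point holds in a limited form. The ideation safety endpoint, as defined, is insensitive to a worsening minority. It may mask an excess of worsening under ENVIE if that arm also has more improvers, a pattern in line with the benefit the trial hopes to show. In the assumed scenarios, sensitivity falls from about 0.86 to 0.28 with equal improvement, and to no signal at all with 10 points more improvers in ENVIE. The sizes rest on assumed shares, a two-level step and complete data at 166 per arm; the direction does not depend on the particular values. Behavioural harm has its own per-arm rate. The sample size and primary analysis are unaffected. The change is worth making because suicidality is the safety parameter the protocol relies on.

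**What to change.** In the Safety endpoints and Safety analyses sections:

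- Add the number and percentage of patients per arm with new or increased C-SSRS ideation severity, relative to a recent (not lifetime) pre-randomisation rating, at each of 3, 6, 9 and 15 months and at any post-baseline visit.
- Use patients with a baseline and at least one post-baseline rating as the denominator, and show the number assessed at each visit.
- Give the between-arm risk difference with its 95% CI.
- Tabulate by arm the patients who met the high-risk trigger already described in the Safety endpoints section.
- Keep the subscore variation as descriptive support.

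Cost: one extra safety table, and a baseline C-SSRS scored for a recent period as well as lifetime, if that is not already done. The any-visit count is sensitive to unequal attendance between arms, so it should be read beside the per-visit counts and numbers assessed.
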